## Abstract

**Background:**

Various sham acupuncture devices have been developed and used in studies on acupuncture. However, there is controversy on whether these devices act as an appropriate placebo or control. In particular, validation of sham acupuncture has only been performed in studies involving healthy individuals. In this regard, questions on the suitability of various sham acupuncture treatments in studies involving disease treatment remain unanswered. Therefore, in this study, we would like to investigate the most appropriate sham acupuncture in the research on treatment of hemiplegic stroke.

**Methods:**

The proposed study is a single-center, prospective, randomized sequence, participant- and assessor-blinded trial with four parallel arms. A total of 90 participants will be randomly assigned to Group 1, Group 2, Group 3, or Group 4 in a 1 : 1 : 1 : 1 ratio. All groups will be treated with Quchi (LI11) for 20 minutes. Group 1 will be treated with verum acupuncture; Group 2, with Park Sham Device; Group 3, with Streitberger's needle; and Group 4, with insertion- and removal-type devices. Participants will undergo one treatment session. The primary outcome is Bang's blinding index. Secondary outcomes are the “Discomfort caused by acupuncture therapy” questionnaire and the Massachusetts General Hospital Acupuncture Sensation Scale index. Immediately after the procedure, all participants will also be monitored for adverse events.

**Discussion:**

This study will help identify the optimal sham acupuncture device that can be used for clinical studies on acupuncture treatment in hemiplegic stroke patients. This trial is registered with KCT0002622.

## 1. Introduction

Acupuncture has been widely used for the treatment of various diseases for decades, not only in Asia but also in the West. Several randomized controlled clinical trials have been conducted to scientifically demonstrate the effectiveness of acupuncture treatments. However, there are conflicting opinions on whether acupuncture treatment has a statistically significant effect in comparison with sham acupuncture (control) in each of the published studies [1]. Several studies have reported that both verum acupuncture and sham acupuncture have a significant therapeutic effect compared with no treatment [2, 3]; in contrast, others have suggested that verum acupuncture is more effective than sham acupuncture [4–6]. There are also some reports that state that verum acupuncture does not have a superior therapeutic effect compared with sham acupuncture [7–9].

Various types of sham acupuncture devices have been used in each study. The most representative type of sham acupuncture device is the Park Sham Device [10], which focuses on the puncture of the needle. In addition, there are other models using Streitberger's needle [11], a needle-foam device [12], and a toothpick [13]. Recently, the insertion and removal model [14] has also been introduced, which distinguishes between verum acupuncture and sham acupuncture, depending on the period of retention of the needle after skin penetration. Finally, the nonacupoint model [15], which focuses on nonacupoints, is also used for sham acupuncture in clinical studies, paying attention to the specificity of the effect on each acupoint.

In the background of the controversy related to the effects of verum acupuncture and sham acupuncture, which can be confirmed through the results of clinical research on various diseases, there is the question “Is the type of sham acupuncture used for each disease suitable for the patient with the disease?” Assessments of the various sham acupuncture treatments have already been conducted [14, 16]. However, these studies have definite limitations because they do not assess sham acupuncture in patients with a specific disease but in healthy individuals without disease. The characteristics of the diseases were not considered in the assessment of sham acupuncture treatment.

In most clinical studies in stroke patients, acupuncture treatment is usually applied to the paralyzed acupoint. However, the paralyzed limbs of stroke patients have complex patterns of muscle tone, muscle strength, and sensory abnormality [17], and there could be differences in the degree of sensitivity during stitching and the discomfort felt during acupuncture treatment compared to those in healthy individuals. Therefore, it is difficult to apply the validation results of sham acupuncture treatments, evaluated in healthy individuals, to stroke patients. However, there has been no study that has evaluated which type of sham acupuncture is suitable for a study population of stroke patients. In addition, even in acupuncture-related clinical trials involving similar stroke types, there are limitations to performing a meta-analysis because of the different types of sham acupuncture treatments used in each study.

In this study, we will evaluate the success rate of blindness and the posttreatment response to sham acupuncture treatments (three types) compared with verum acupuncture treatment in hemiplegic stroke patients. To assess the success blinding rate of various sham acupuncture treatments, a randomized, double-blinded (participants and evaluator), 4 group paralleled clinical trial will be conducted. Through this study, we aim to explore the most appropriate sham acupuncture tool for clinical research on stroke.

## 2. Methods

### 2.1. Objectives

The objectives of this study are to explore the most suitable acupuncture tool for the clinical study of stroke patients. Therefore, the success rate of the blinding will be determined, and the posttreatment response to sham acupuncture treatments (three types) compared with real acupuncture treatments in patients with hemiplegic stroke will be assessed.

### 2.2. Study Setting and Trial Design

We will conduct this study at the Kyung Hee University Korean Medicine Hospital. This study has been approved by the Institutional Review Board of Kyung Hee University Korean Medicine Hospital (KOMCIRB-170717-HR-020). If the protocol requires modifications, it will be approved by the Institutional Review Board of Kyung Hee University Korean Medicine Hospital. Written informed consent will be obtained from all participants by designated clinical research coordinator (CRC). Patient confidentiality will be ensured before, during, and after the trial.

This study will be a single center, prospective, randomized, evaluator-participant double-blinded trial with four parallel arms: arm 1 (Group 1), arm 2 (Group 2), arm 3 (Group 3), and arm 4 (Group 4). Each participants will be randomly assigned.

### 2.3. Inclusion and Exclusion Criteria

Participants who meet the following criteria will be included: (1) 19 years or older; (2) diagnosed with cerebral hemorrhage or cerebral infarction through brain computed tomography (CT) or magnetic resonance imaging (MRI); (3) weakness or hemiparesis or hemiplegia due to cerebral hemorrhage or cerebral infarction, with a Modified Ashworth Scale (MAS) score of 2 points or less; (4) stable vital signs; and (5) voluntary participation in this study.

The following participants are excluded: (1) patients with unconsciousness, aphasia, and cognitive dysfunction (Mini-Mental State Examination-Korean version (MMSE-K) <24); (2) those with a past history of brain disease (e.g., previous stroke, mental illness, consciousness disorder due to head trauma, previous brain surgery, or spastic disease); (3) those with severe heart, liver, or kidney disease or bleeding disorders; (4) those with other serious diseases (e.g., cancer, dementia (Alzheimer's disease or dementia of Lewy body), Parkinson's disease, and Parkinson's syndrome); (5) those with subarachnoid hemorrhage; (6) those who had received acupuncture treatment for hemiplegia, hemiparesis, and weakness owing to previous stroke; (7) those with needle phobia; and (8) pregnant or lactating female patients.

### 2.4. Recruitment Strategies

We plan to recruit participants from among the inpatients through poster advertisement on the bulletin boards of the hospital. Potential participants will call an investigator and be prescreened for eligibility. The participants of this study should be selected from the applicants who meet all the criteria but do not qualify for any of the exclusion criteria. Even if the results of clinical laboratory testing of potential participants show minor transient abnormalities, they could be selected as eligible participants if an investigator determines that such changes have little influence on the study and are not harmful to the participant. Eligible participants will make an appointment. At the first meeting with a CRC, information about the study (risks and benefits of the study) will be provided. After this procedure, potential participants will sign an informed consent form, if they agree to enroll in this study. The registration number of the study is assigned to all eligible participants.

### 2.5. Randomization and Allocation Concealment

After registration, the participants will be randomized to Group 1, Group 2, Group 3, or Group 4. Group 1 will receive verum acupuncture; Group 2 will receive Park Sham Device acupuncture; Group 3 will receive Streitberger's needle acupuncture; and Group 4 will receive insertion- and removal-type acupuncture. In this allocation, the stratified-block randomization will be conducted by an independent CRC. The stratification is performed according to whether there is a sensory disturbance of the affected limb (1: no sensory disturbance; 2: sensory disturbance). Block lengths are eight. Random assignment will be conducted by computer-based randomization. The block random function of R software (version 3.1.2) will be used to generate a random number. The assignment probability of the treatment group and the three control groups is 1 : 1 : 1 : 1. For allocation concealment, an independent CRC places the random assignment code in an impermeable envelope and seals it, and it is then delivered to the practitioner. The practitioner will open the random assignment envelope in front of the participant and assign the participant. After that, practitioners will keep the opened envelopes with themselves.

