### 2.6. Blinding

The participants and the evaluator will be blinded in this trial. All participants will be blinded to the types of acupuncture. After the treatment, an independent, blinded evaluator who does not know the group assignment will conduct the outcome evaluation. The researcher who will oversee the statistical analysis will also be blinded so that the treatment for each group remains unknown. However, it is almost impossible to blind the practitioners who conduct acupuncture. Therefore, the practitioner will be forbidden from discussing the type of acupuncture with the participants.

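### The unblinded practitioner opens the assignment envelope in front of the participant, and no stated safeguard covers that step, although the participant's guess is the primary outcome

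*Protocol article*

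**What the plan says.** Section 2.5 of the protocol article describes the allocation step. For concealment, "an independent CRC places the random assignment code in an impermeable envelope and seals it, and it is then delivered to the practitioner". It continues: "The practitioner will open the random assignment envelope in front of the participant and assign the participant".

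Section 2.6 sets the blinding requirement: "All participants will be blinded to the types of acupuncture". It accepts that the practitioner cannot be masked ("it is almost impossible to blind the practitioners who conduct acupuncture") and gives one behavioural safeguard: "the practitioner will be forbidden from discussing the type of acupuncture with the participants".

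Section 2.7.1 adds a physical safeguard, a visual barrier that keeps participants from seeing their arm while the procedure is under way. Section 2.7.2 repeats that the barrier hides the arm.

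Section 2.8.1 makes the participant's belief about verum or sham, collected straight after treatment, the basis of the primary outcome, Bang's blinding index. On the protocol's scale 0% is random guessing and 100% is complete unblinding. Section 2.10 plans at least 22 participants per group and 90 in total.

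**The concern.** In most sham-controlled trials a weakness in participant blinding threatens the outcome indirectly. Here blinding is itself the outcome. The index is meant to show how well each device hides its nature from a stroke patient. A cue from any other source is indistinguishable from a cue given by the device.

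The allocation step places such a source beside the participant. An unblinded person opens the code and reads it with the participant present. A glimpse of the code, or the practitioner's reaction to it, could inform the guess given soon afterwards. Participants who learned their arm this way would be counted as unblinded by the needle. The index would be biased upwards, and nothing in the collected data would separate leakage from device failure.

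**Working it through.** **1. Does any stated safeguard cover the step?**

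| Element | Source | Covers the opening of the envelope? |
|---|---|---|
| Sealed, impermeable envelope | 2.5 | Only until it is opened |
| Ban on discussing the needle type | 2.6 | Covers speech about the type; not sight of the code or a non-verbal reaction |
| Visual barrier | 2.7.1, 2.7.2 | Described as hiding the arm during the procedure; not described as shielding the envelope |
| Masked or unintelligible code | not stated | Cannot be assumed |

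No stated safeguard applies to the moment when the code is read in the participant's presence.

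**2. The plan's own figure.** 4 × 22 = 88, and 90 − 88 = 2 for withdrawal (2/90 = 2.2%). The stated total of 90 is reproduced. The point does not depend on it, but the 22 per arm sets the precision used below.

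**3. Effect of a leak on the index.** With no 'do not know' answers, BI = 2 × P(correct) − 1. Let a share x of an arm learn its allocation and answer correctly, while the rest have the index b that the device alone would give. Then

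observed BI = x + (1 − x)b, so the shift is x(1 − b).

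The documents give no value for x or b, so both are assumptions, shown over a range:

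| x | b = −0.50 | b = 0 | b = +0.30 |
|---|---|---|---|
| 5% | −0.425 | +0.05 | +0.335 |
| 10% | −0.35 | +0.10 | +0.37 |
| 20% | −0.20 | +0.20 | +0.44 |
| 30% | −0.05 | +0.30 | +0.51 |
| 50% | +0.25 | +0.50 | +0.65 |

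(0.10 here is 10 points on the protocol's percentage scale.)

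**4. Precision.** At BI = 0 with 22 answers, SE = 1/√22 = 0.213, and the 95% half-width is 1.96 × 0.213 = 0.42. A shift of 0.10 to 0.20 lies well inside this, so the data could not reveal it.

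**5. Chance of a false alarm.** As an illustration, call an arm unblinded if at least 16 of 22 guesses are correct. Under random guessing, P = 0.026. With leakage alone (b = 0), P(correct) = 0.5 + x/2, and the chance of the call becomes 0.07 at x = 10%, 0.16 at x = 20% and 0.30 at x = 30%. This rule is mine, not the protocol's.

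**The case against.** The strongest reply is that the article never says the participant is shown the code or could read it. The envelope holds an assignment code, which may mean nothing to a patient, and opening a sealed envelope before the participant may simply show that the seal was intact. The order of envelope and barrier is not given either. The flow and room figures are not visible here, and the operating procedure mentioned in Section 2.12 is not at hand. This stands: the text opens a route for exposure and does not establish that exposure occurs. With a masked, shielded code the leak could be small.

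A second reply is that a leak common to all sham arms preserves their order. Since x + (1 − x)b rises with b, a common x raises the values and shrinks differences by the factor 1 − x, but the ranking remains. This also stands. The objective in Section 2.1 is to find the most suitable device, so a common leak would bias the absolute indices and not the ordering.

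A reader might also infer three stronger claims, which the documents do not support:

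- *Leakage differs by arm because the kits look different.* Table 1 says that the appearance in the control groups matches Group 1, and it lists the same needle from the same maker for Groups 1 and 4.
- *The fixed block length gives allocations away.* Section 2.5 does say "Block lengths are eight". With two per arm, the eighth allocation is always determined and the seventh in 1 of 7 blocks, so (1 + 1/7)/8 = 14% are known in advance to someone tracking each stratum. But the practitioner is openly unblinded and has no stated enrolment role: an investigator prescreens, a coordinator obtains consent, and randomisation follows registration. Knowing a code shortly before opening it changes nothing in the participant's guess.
- *Keeping the envelopes is harmful* ("practitioners will keep the opened envelopes with themselves"). The single practitioner of Section 2.7.1 treated those participants and already knows their arms.

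**Conclusion.** The point holds in a limited form. Section 2.5 prescribes reading the allocation in the presence of the person who must not learn it, and the safeguards in Sections 2.6 and 2.7.1 do not extend to that moment. Because that person's guess is the primary outcome, any cue would pass directly into Bang's index and be attributed to the device.

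The size is conditional. It depends on an assumed leakage share, on leaked participants answering correctly, and on no 'do not know' answers. For 10% to 20% leakage from a true index of 0, the shift is +0.10 to +0.20, against a 95% half-width of about 0.42. It would be larger from a negative true index: +0.30 at 20% leakage from −0.50. The documents do not show that the allocation is in fact disclosed, or that the ranking of devices would be reversed. The case for correcting the step is that a leak could not be identified or removed after data collection, while preventing it is cheap.

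**What to change.** Change Section 2.5, and the operating procedure to match, so that the practitioner opens the envelope and prepares the assigned device out of the participant's sight and hearing. The visual barrier should be in place before the practitioner approaches. Section 2.7.1 should then give this order explicitly: barrier set, envelope opened elsewhere, device prepared, practitioner approaches.

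The cost is about a minute of extra set-up per participant and one revised step in the procedure. Sample size, outcomes, treatments and the randomisation list are unaffected. This point calls for no change to the block length or to who keeps the envelopes.

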### 2.6. Blinding

The participants and the evaluator will be blinded in this trial. All participants will be blinded to the types of acupuncture. After the treatment, an independent, blinded evaluator who does not know the group assignment will conduct the outcome evaluation. The researcher who will oversee the statistical analysis will also be blinded so that the treatment for each group remains unknown. However, it is almost impossible to blind the practitioners who conduct acupuncture. Therefore, the practitioner will be forbidden from discussing the type of acupuncture with the participants.

### 2.7. Interventions

#### 2.7.1. Study Flow and Treatment Procedure

Acupuncture treatment will be performed once during the trial. The acupuncture treatment will be carried out by a practitioner with more than 2 years of clinical experience. Before the treatment procedure, the patient's basic characteristics (e.g., age, sex, body mass index (BMI), vital signs, past medical history, drug consumption, education, occupation, alcohol consumption, smoking habit, and stroke type (cerebral infarction or cerebral hemorrhage), MMSE-K, National Institute of Health Stroke Scale (NIHSS) score, and Modified Rankin Scale will be investigated.

The entire procedure will be performed over 20 minutes. After all of the preparations for treatment are complete, the participants will be asked to lie on the bed for 2–5 min to stabilize. In the verum acupuncture group, real manual acupuncture will be performed. In the three sham acupuncture groups, Park Sham Device, Streitberger's needle, or insertion- and removal-type acupuncture will be applied. Details of the acupuncture treatment are described in the Standards for Reporting Interventions in Clinical Trials of Acupuncture (STRICTA) checklist in Table 1. During the entire trail period, all the procedures of acupuncture will be carried out by one practitioner who is independent. During the procedure, a prepared visual barrier will prevent participants from viewing their arm and confirming the type of acupuncture. Immediately after the end of the procedure, a questionnaire for determining Bang's blinding index and the “Discomfort caused by acupuncture therapy” questionnaire will be administered, and the Massachusetts General Hospital Acupuncture Sensation Scale (MASS) index, by deqi sensation, will be determined (Figure 1).

#### 2.7.2. Acupuncture Treatment Setting

The acupuncture treatment room setting will be a modification of that in a previous study by Leem et al. [16] and is shown in Figure 2. Participants will lie on the bed in a supine position. A visual barrier will prevent participants from viewing their arm to ensure blindedness.

### 2.8. Outcome Assessments

#### 2.8.1. Primary Outcome

Immediately after the end of the procedure, a questionnaire will be administered to assess the success of blindedness, and the results were used to obtain Bang's blinding index (BI) [18]. The questionnaire is organized as follows: (i) strongly believe the treatment is verum acupuncture, (ii) somewhat believe the treatment is verum acupuncture, (iii) somewhat believe the treatment is sham acupuncture, (iv) strongly believe the treatment is sham acupuncture, and (v) do not know. The BI value ranges from −100 to 100%. A value of 0% represents random guessing (for example, 50% accurate and 50% inaccurate), 100% represents complete unblinding (for example, all answers are accurate), and −100% represents the opposite of guessing (for example, all responses are incorrect).

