### 2.11. Statistical Analysis

Hypothesis to be tested in this study is that the certain sham device will reveal the most similar sensation to verum acupuncture in the affected limb of stroke patients. Primary outcome of this study is Bang's blinding index in each group. The value of Bang's blinding index of each sham acupuncture device will be calculated by comparison with the verum acupuncture group. This statistical process will be based on Bang's previous study, published in 2004 [18]. In secondary outcome analysis, the values of “Discomfort caused by acupuncture therapy” five questions and MASS index will be compared by ANOVA. In baseline characteristics, categorial variables will be compared by a chi-square test and continuous variables will be compared by ANOVA. A comparative analysis of the frequency of patients with sensory disturbances by each group will evaluate whether stratification assignments have been made properly. In subgroup analysis, we will compare the values of primary and secondary outcomes in patients with sensory disturbances. Patients with sensory disturbances are defined as patients who complaint sensory disturbances such as numbness, hypesthesia, or paraesthesia in affected limbs. In this study, sensitivity analysis will not be performed. A 5% significance level will be used. Study data will be analyzed using the Statistical Package for the Social Sciences (SPSS) software, version 16.0, for Windows and Microsoft Excel 2010 for windows by a blinded statistician.

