**Figure 2 fig2:**
[figure not shown]
Acupuncture treatment setting.

**Table 1 tab1:** STRICTA checklist (details of intervention).

	Item	Details
1. Acupuncture rationale	Style of acupuncture	Manual acupuncture based on traditional Korean medicine theory
	Reasoning for treatment provided, based on historical context, literature sources, and/or consensus methods, with references wherever appropriate	Acupuncture points to be used in this study were Quchi (LI11) located at the elbow of the affected upper limb. According to a review of systematic literature review and meta-analysis of existing strokes [18], one of the most commonly used acupuncture points for stroke treatment is Quchi
	Extent to which treatment was varied	All participants will receive standardized treatment

2. Details of needling	Number of needle insertions per subject per session	1
	Names of points used	Quchi (LI11) at the affected side
	Depth of insertion, based on a specified unit of measurement	5–10 mm
	Response sought	Simple puncture
	Needle stimulation	Manual acupuncture
	Needle retention time	20 minutes
	Needle type	Group 1: verum acupuncture needle; 0.25 × 40 mm sterilized stainless steel needle (Dong Bang acupuncture, Gyeonggi-do, Korea)

3. Treatment regimen	Number of treatment sessions	1 time
	Frequency and duration of treatment sessions	20 minutes for 1 time

4. Other components of treatment	Details of other interventions administered to the acupuncture group	None
	Setting and context of treatment, including instructions to practitioners, and information and explanations to patients	The study will be conducted in the Kyung Hee University Korean Medicine Hospital and all information will be provided to the subjects

5. Practitioner background	Description of participating acupuncturists	A KMD after completing 6 years of Korean medicine undergraduate course or KM internal medicine specialists who have at least two years of clinical experience

6. Control or comparator interventions	Rationale for the control or comparator in the context of the research question, with sources that justify this choice	Validated placebo acupuncture devices will be used in control groups

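### The primary blinding index is defined within each arm, but Section 2.11 wants each sham compared with verum; 0% in a sham arm does not show that it matches verum, and the contrast should be defined

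*Protocol article*

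**What the plan says.** Section 2.11 names the primary endpoint: "Primary outcome of this study is Bang's blinding index in each group". Section 2.8.1 gives its scale: "The BI value ranges from −100 to 100" per cent, with all answers correct at the top and all incorrect at the bottom. For the midpoint it says "A value of 0% represents random guessing (for example, 50% accurate and 50% inaccurate". Participants choose among two verum answers, two sham answers and a neutral one; the second half of the list reads "iii) somewhat believe the treatment is sham acupuncture, (iv) strongly believe the treatment is sham acupuncture, and (v) do not know".

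Section 2.11 states the hypothesis as one of likeness: one of the sham devices will feel closest to verum in the affected limb. It adds that the index of "each sham acupuncture device will be calculated by comparison with the verum acupuncture group", refers to the cited source for the method, and gives no formula for the comparison.

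On allocation, Section 2.5 says "The assignment probability of the treatment group and the three control groups is 1 : 1 : 1 : 1", so three of the four arms are sham. On what participants are told, Table 1 (item 4) says only that "all information will be provided to the subjects".

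**The concern.** The trial asks which sham is most like verum. The only interpretive scale given for the primary outcome answers a different question: how far answers within one arm depart from an even split of right and wrong. The two coincide only if participants, absent any informative sensation, are equally likely to answer verum or sham. Nothing in the design ensures that. A shared lean in either direction moves a perfect sham away from 0%, and a sham at 0% may still be easy to tell from verum. The sentence in Section 2.11 that points to verum cannot be carried out with the index as Section 2.8.1 describes it. A reader who ranks devices on the stated scale could therefore favour one whose recipients do not answer like verum recipients.

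**Working it through.** **Inputs.** Anchors 0%, 100% and −100% (Section 2.8.1); one verum and three sham arms, equal allocation (Section 2.5); at least 22 per group (Section 2.10). Assumption: a do-not-know answer counts as neither correct nor incorrect.

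**1. The plan's own anchors.** Take BI = P(correct) − P(incorrect) within an arm.
- 50/50: 0.5 − 0.5 = 0
- all correct: 1 − 0 = +1
- all incorrect: 0 − 1 = −1

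All three stated anchors are reproduced. Neither the allocation ratio nor any other arm enters the formula.

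**2. A perfect sham need not score 0%.** Let a share q answer verum in both arms, with no do-not-know answers. Then BI(sham) = (1 − q) − q = 1 − 2q and BI(verum) = 2q − 1.

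| q | BI(sham) | BI(verum) | Sum |
|---|---|---|---|
| 0.25 | +50% | −50% | 0 |
| 0.40 | +20% | −20% | 0 |
| 0.50 | 0% | 0% | 0 |
| 0.60 | −20% | +20% | 0 |
| 0.75 | −50% | +50% | 0 |

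The row q = 0.25 would arise if participants knew that three of four arms are sham and guessed in that proportion. The row q = 0.75 would arise if most believed they had been needled, whatever they knew of the odds.

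**3. A sham at 0% need not resemble verum.** Let 50% of a sham arm and 90% of the verum arm answer verum. Then BI(sham) = 0% and BI(verum) = 0.9 − 0.1 = +80%, a gap of 40 points in the share answering verum. At n = 22 the sham arm's 95% Wald interval contains 0 with probability about 0.95. A direct 22 v 22 comparison has power of about 0.85 at that gap, and about 0.40 if 75% of the verum arm answer verum.

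**4. Effect on a ranking (illustration).** Let 80% of verum recipients answer verum, 75% with device X and 50% with device Y.
- BI(X) = 1 − 1.5 = −50%; BI(Y) = 0%. On the Section 2.8.1 scale, Y looks ideal.
- X is 5 points from verum; Y is 30 points from verum.
- With BI(verum) = +60%, the sums are +10% for X and +60% for Y, so the order reverses.

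**5. A contrast that answers the question.** Write v and s for the shares answering verum and sham in a sham arm, and v0 and s0 for those in the verum arm. Then D = BI(verum) + BI(sham) = (v0 − s0) − (v − s). If participants cannot tell the two apart, D = 0 whatever q is, as the last column in step 2 shows.

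**6. Precision at 22 per arm**, with indices near 0 and no do-not-know answers. SE(BI) = 1/√22 = 0.213, so the half-width is 1.96 × 0.213 ≈ 0.42. For D it is 0.418 × √2 ≈ 0.59.

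**The case against.** The strongest defence has three parts.

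- **The 0% anchor is correct.** This stands. A reader might infer that equal allocation to one verum and three sham arms makes 50/50 the wrong reference. It does not: allocation is absent from the formula and can shift guessing only through participants' beliefs. The +50% figure needs participants who know the odds and guess in proportion. The article does not say whether they are told, the Table 1 entry is generic, and Section 2.4 mentions only risks and benefits. If participants guess evenly, 0% is the right chance level despite the three sham arms. The error in step 3 does not come from the ratio at all.

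- **The plan has no rule to misfire.** This also stands. A reader might infer that the plan would declare a good sham unblinded. No section tests the index against 0, sets a cut-off, or ranks devices by closeness to 0. If such a Wald test were applied at n = 22 and q = 0.25, the sham interval would lie above 0 with probability 0.70 (about 0.52 for an exact binomial test). That falls to 0.63 with 20% do-not-know answers, 0.50 with 40%, and 0.16 at q = 0.40 with none. These are conditional illustrations, not error rates of this plan.

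- **Section 2.11 already points to verum, and details may sit in a fuller document.** This stands in part. The intention is visible and a formula may be left to an analysis plan. But the article does fix a within-arm scale and then describes a between-arm calculation of the same quantity. That mismatch is in the text itself.

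**Conclusion.** Sections 2.8.1 and 2.11 do not fit together on the primary outcome. The within-arm index is correctly anchored, but its distance from 0% does not measure likeness to verum, which is the stated hypothesis. With indistinguishable devices and no do-not-know answers, the sham index is 1 − 2q. It runs from +50% to −50% as the common share answering verum goes from 0.25 to 0.75, and do-not-know answers shrink these values (to +40% at q = 0.25 with 20% of them). In the other direction, 0% in a sham arm is compatible with a 40-point gap from verum.

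The documents do not support the claim that the allocation ratio invalidates the 0% reference, or that the primary result will select the wrong device. The finding is that the stated scale allows a misleading reading, and that a better-targeted contrast is available from the same data.

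**What to change.** 1. In Section 2.11, keep the per-arm index as description. Replace the sentence on comparison with verum by the primary contrast D = BI(verum) + BI(sham) for Groups 2, 3 and 4, each with a 95% confidence interval.
2. Compare the devices on |D| together with its interval. At this sample size an interval that includes 0 does not establish equivalence.
3. In Section 2.8.1, keep the three anchors and add that 0% in a sham arm alone does not show equivalence to verum.
4. Report the do-not-know share by arm beside D, because D compares net belief and can be 0 when those shares differ.

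The questionnaire, participants and sample size are unchanged, and D does not require settling what participants know about the odds. The cost is wording in two sections and a wider interval: about ±0.59 for D against ±0.42 for a single-arm index at 22 per arm.
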